## Abstract

**Background:**

Cardiac surgery-associated acute kidney injury (CSA-AKI) is a serious complication in patients undergoing cardiac surgery with extracorporeal circulation (ECC) that increases postoperative complications and mortality. CSA-AKI develops due to a combination of patient- and surgery-related risk factors that enhance renal ischemia–reperfusion injury. Sodium-glucose cotransporter 2 inhibitors (SGLT2i) such as empagliflozin reduce renal glucose reabsorption, improving tubulo-glomerular feedback, reducing inflammation and decreasing intraglomerular pressure. Preclinical studies have observed that SGLT2i may provide significant protection against renal ischemia–reperfusion injury due to their effects on inadequate mitochondrial function, reactive oxygen species activity or renal peritubular capillary congestion, all hallmarks of CSA-AKI. The VERTIGO (EValuating the Effect of periopeRaTIve empaGliflOzin) trial is a Phase 3, investigator-initiated, randomized, double-blind, placebo-controlled, multicenter study that aims to explore whether empagliflozin can reduce the incidence of adverse renal outcomes in cardiac surgery patients.

**Methods:**

The VERTIGO study (EudraCT: 2021-004938-11) will enroll 608 patients that require elective cardiac surgery with ECC. Patients will be randomly assigned in a 1:1 ratio to receive either empagliflozin 10 mg orally daily or placebo. Study treatment will start 5 days before surgery and will continue during the first 7 days postoperatively. All participants will receive standard care according to local practice guidelines. The primary endpoint of the study will be the proportion of patients that develop major adverse kidney events during the first 90 days after surgery, defined as ≥25% renal function decline, renal replacement therapy initiation or death. Secondary, tertiary and safety endpoints will include rates of AKI during index hospitalization, postoperative complications and observed adverse events.

**Conclusions:**

The VERTIGO trial will describe the efficacy and safety of empagliflozin in preventing CSA-AKI. Patient recruitment is expected to start in May 2024.

KEY LEARNING POINTS
**What was known:**
Cardiac surgery-associated acute kidney injury (CSA-AKI) is a life-threatening complication that affects almost half of patients undergoing cardiac surgery with extracorporeal circulation and is associated with higher incidence of postoperative complications and mortality.Although several preventive strategies have been tested to reduce the high rates of CSA-AKI, none has achieved convincing enough results to integrate these therapies in daily clinical practice.
**This study adds:**
Sodium-glucose cotransporter 2 inhibitors are a class of oral antidiabetic drugs that have demonstrated significant nephroprotective effects, slowing the progression of chronic kidney disease, as well as reducing proteinuria.The VERTIGO (EValuating the Effect of periopeRaTIve empaGliflOzin) trial aims to describe the effect of perioperative empagliflozin to reduce the incidence of CSA-AKI in patients that require elective cardiac surgery.
**Potential impact:**
The trial will provide evidence about the efficacy and safety of empagliflozin in reducing the incidence and severity of CSA-AKI.If results are favorable, the planned intervention could be widely applied as a preventive therapeutic strategy in this clinical setting.

## INTRODUCTION

Cardiac surgery-associated acute kidney injury (CSA-AKI) is a serious complication that affects up to 40% of patients undergoing cardiac surgery with extracorporeal circulation (ECC). This complication is associated with higher incidence of postoperative complications and mortality, longer in-hospital stay and increased healthcare costs [1].

The combination of risk factors such as age, patient comorbidities such as hypertension, diabetes or peripheral artery disease, together with other determinants associated with surgery itself, such as time on ECC, aortic cross-clamp time or high-dose inotrope administration, explain the high incidence of CSA-AKI [2]. The joint action of these risk factors induces systemic and renal tissue ischemia, increased oxidative stress and inflammation [3].

Kidneys are especially vulnerable to ischemia, which occurs in two phases: during the initial phase, ischemia triggers nutrient and oxygen supply reduction, causing kidney cell injury and death [4]. An intense inflammatory response develops during the second, reperfusion phase, which intensifies tissue damage and leads to acute renal failure [5].

Over the last few years, several preventive strategies have been tested aiming at reducing the high rates of CSA-AKI and its consequences, including the use of albumin, erythropoietin or remote ischemic preconditioning, without achieving conclusive enough results to allow the integration of these therapies in daily clinical practice [6–8].

Sodium-glucose cotransporter 2 inhibitors (SGLT2i) are a class of oral antidiabetic drugs that inhibit renal glucose reabsorption in the proximal tubule of the nephron, increasing renal glucose excretion, improving tubulo-glomerular feedback by inducing efferent arteriole vasodilation and decreasing intraglomerular pressure. The consequence of these changes is a significant short- and long-term nephroprotective effect [9, 10].

SGLT2i induce a fasting-like state that facilitates fatty acid β-oxidation, body adiposity reduction and ketone formation [11]. Glycosuria resulting from SGLT2i administration reduces plasma glucose and insulin levels, creating an energy-deficient metabolic state that stimulates the synthesis of ketones such as β-hydroxybutyrate that can be used as an alternative energy source. This molecule has significant antioxidant and anti-inflammatory effects due to its capacity to activate the hydroxycarboxylic acid receptor 2, stimulate anti-inflammatory macrophage subpopulations and the formation of prostaglandin E2, or modulate the activity of antioxidant enzymes such as catalase or manganese superoxide dismutase [9, 12–14]. β-Hydroxybutyrate is also capable of protecting mitochondrial function and inhibiting hydroxyl radical activity that boosts oxidative stress–associated damage [15, 16]. Depleted levels of prostaglandin E2 or superoxide dismutase 1 concentrations in kidney tissue, as well as reduced mitochondrial abundance, have been associated with more severe ischemic AKI [17–19].

In parallel to their effect on ketone formation, SGLT2i have additional anti-inflammatory properties that generate synergistic effects, such as the inhibition of the NOD-like receptor Pyrin domain containing protein 3 (NLRP3) inflammasome, the modulation of metabolites of the tricarboxylic acid cycle or the reduction of reactive oxygen species activity [20, 21]. Persistent overexpression of NLRP3 has been associated with the severity of ischemia–reperfusion-induced AKI [22]. In animal models of renal ischemia, SGLT2i stimulated the expression of hypoxia-inducible factor 1 (HIF-1), reducing the Bax/Bcl2 ratio in renal tissue, improving renal function and reducing apoptosis [23]. It has also been observed that SGLT2i prevented ischemia–reperfusion-associated renal peritubular capillary congestion and hemorrhage [24].

Results of the recent EMPA-KIDNEY (The study of heart and kidney protection with empagliflozin) and DAPA-CKD (A study to evaluate the effect of dapagliflozin on renal outcomes and cardiovascular mortality in patients with chronic kidney disease) trials have demonstrated the ability of SGLT2i to reduce proteinuria in chronic kidney disease, considerably slowing its progression [25, 26]. The fundamentals for such effect, including downregulation of proinflammatory and profibrotic pathways in the tubule or decreased energy expenditure via Na+/K+ ATPase and Na+/H+ exchanger 3, could perfectly well apply to ischemic AKI [27].

SGLT2i have shown great preclinical potential against ischemia–reperfusion injury in multiple organs—including the kidney—and with a wide administration window, from 7 days to 2 h before ischemia–reperfusion injury. This effect seems to be mediated through several mechanisms, such as increased renal levels of glycogen synthase kinase 3β, restoration of urinary levels of microRNA-26a, or a downregulation in ischemic tissue of the expression of proinflammatory markers such as interleukin-1, interleukin-6 or tumor necrosis factor-α [28–30].

There are no published data regarding key points of the study, such as the minimum effective dose of empagliflozin as a preventive therapy for CSA-AKI or the most appropriate timing for therapy initiation. Furthermore, SGLT2i have been considered as “sick days drugs,” with some guidelines recommending against their routine use during hospital stays [31]. Nevertheless, results of empagliflozin administration in patients admitted in intensive care/cardiac care units have already been reported, with an acceptable safety profile [32, 33]. The results of our study will provide key data regarding the efficacy and safety of empagliflozin in this setting. A dose of empagliflozin 10 mg has been chosen, since it has shown both long-term nephro- and cardio-protective efficacy, with a low incidence of adverse effects [25, 34].

The aim of this trial is to analyze the effect of the perioperative administration of empagliflozin 10 mg in patients who will undergo elective cardiac surgery with ECC on kidney function, inflammation, oxidative stress, postoperative complications and mortality. To do this, we have designed a Phase 3, investigator-initiated, randomized, double-blind, placebo-controlled, multicenter study.

## MATERIALS AND METHODS

### Study objective

The primary aim of the VERTIGO (EValuating the Effect of periopeRaTIve empaGliflOzin) trial is to evaluate whether perioperative empagliflozin reduces the composite endpoint of worsening of renal function, defined as a decline in estimated glomerular filtration rate (eGFR) of ≥25%, renal replacement therapy initiation or death during the first 90 days following surgery, compared with placebo, in patients requiring elective cardiac surgery with ECC. Furthermore, the trial will evaluate the effects of empagliflozin, compared with placebo, on postoperative AKI severity, postoperative complications, length of intensive care unit and in-hospital stay, as well as need for hospital readmission for cardiovascular disease, patient-reported quality of life and safety profile of empagliflozin in this setting. This study will be conducted in accordance with the declaration of Helsinki and the International Council for Harmonisation Guidelines on Good Clinical Practice, and has been designed following the recommendations of the COMET Handbook and the SPIRIT 2013 Statement [35, 36]. The first patient will be enrolled in May 2024 and study completion is expected in approximately December 2025. The trial is registered with https://eudract.ema.europa.eu (EudraCT: 2021-004938-11).

### Study design

VERTIGO is a Phase 3, investigator-initiated, randomized, double-blind, placebo-controlled, multicenter study that will recruit 608 patients at four third-level, academic hospitals. Figure 1 shows the overall study design.

**Figure 1: fig1:**
[figure not shown]
VERTIGO study design. ICU, intensive care unit.

### Trial participants

Trial participants will be adults that require elective cardiac surgery with ECC with a baseline eGFR >30 mL/min/1.73 m^2^. Added inclusion and exclusion criteria are indexed in Table 1.

**Table 1: tbl1:** Inclusion and exclusion criteria.

Inclusion criteria
- ≥18 years of age
- Requiring elective cardiac surgery with ECC
- Able to understand the aim of the study and to provide written informed consent
Exclusion criteria
- Emergent surgery
- Endocarditis
- Patients awaiting heart transplantation
- Planned use of intra-aortic balloon pump
- Type 1 diabetes
- Chronic kidney disease with eGFR <30 mL/min/1.73 m^2^
- Severe liver dysfunction (ALT or AST >3 times above the upper limit of normality)
- Active cancer
- Active treatment with any SGLT2i
- Known allergy to empagliflozin, any other SGLT2i or any of its excipients
- Solid organ transplant recipients
- Pregnant or lactating women
- Patients who are participating in another clinical trial

ALT, alanine transaminase; AST, aspartate transaminase.

### Enrolment

Potentially eligible patients will be invited for screening. Those who meet all inclusion criteria, and no exclusion criteria will be randomized within 3 days after the screening visit.

### Randomization, stratification and blinding

Patients meeting all eligibility criteria will be randomized in a 1:1 ratio to receive either empagliflozin 10 mg orally daily or matching placebo in a double-blind manner. These patients will constitute the primary intention-to-treat population for evaluating the efficacy and safety of the planned intervention. Randomization will be performed centrally employing an interactive web system with a computer-generated randomization schedule and will be stratified according to study site and diabetic status (yes/no) to ensure a similar proportion of patients with and without type 2 diabetes in both treatment groups. Block randomization with random block sizes will be employed to minimize selection bias. Planned enrolment is 608 patients from four sites.

All patients and study personnel, except for the independent data-monitoring committee, will be kept blinded to treatment allocation. Empagliflozin and placebo will be packaged in an indistinguishable manner, with identical appearance and labelling. Study medication will be administered in the morning, except for the sixth dose (first postoperative dose), at approximately the same time of the day throughout the study.

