### Schedule of assessments

The first study visit will be performed immediately after study participants provide written informed consent, enrolment and randomization. Anthropometric information, baseline treatment and laboratory data will be recorded. Elective cardiac surgery will be programmed within 30 days of the first visit. The research team will provide study medication to each participant. Doses 1–5 of study medication will be administered daily on the last 5 days before surgery (Days –5 to –1). The sixth dose will be administered within the first 8 h after surgery (Day 0). Doses 7–13 will be administered daily during the first 7 days after surgery (Fig. 1). Previous research has not adequately defined the best timing for SGLT2i initiation to prevent ischemia–reperfusion injury with protocols starting SGLT2i administration both before and after the onset of injury [21, 23, 24]. However, empagliflozin has been shown to reach the peak of its glycosuric effect within the first 24 h after its administration, with further stabilization over the next 72 h. Moreover, renal protective effects of SGLT2i seem to appear early after treatment initiation [23, 37]. We chose to start study medication 5 days before surgery to ensure a stable and sustained effect of empagliflozin on the kidney.

The visit schedule is summarized in Fig. 2. Vital signs, blood and urine samples, as well as information about study endpoints, adverse events and other outcomes of interest, will be recorded in each visit.

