Primary endpoint analysis will be based on the intention-to-treat population, defined as all validly randomized patients. In the analysis of the primary endpoint, study treatments will be compared using a Cox proportional hazards regression model with a factor for the treatment group. Hazard ratio, 95% confidence interval and *P*-value will be reported. Kaplan–Meier estimates of the cumulative incidence to the occurrence of MAKE90 will be calculated. Secondary endpoints will be tested in a similar manner. If superiority is achieved for the primary endpoint, the secondary endpoints will be tested following a hierarchical order, as follows. (i) Any stage of AKI defined according to Kidney Disease: Improving Global Outcomes (KDIGO) guidelines during index admission. (ii) Stage 3 AKI according to KDIGO guidelines during index admission. (iii) Time to renal replacement therapy initiation during index admission. (iv) Time to death from any cause. Statistical significance will be required before testing the next hypothesis in the hierarchy. The effects of the planned intervention on primary and secondary outcomes will also be assessed in subanalyses stratified by sex, baseline eGFR, diabetic status and type of planned surgery (valvular/coronary/valvular and coronary).

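### Safety is assigned to the intention-to-treat population although dosing may start up to 25 days after randomisation, so never-dosed patients shrink the adverse-event difference between arms

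*Protocol article*

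**What the plan says.** The protocol article, under Randomization, stratification and blinding, refers to the patients randomised 1:1 and states: "These patients will constitute the primary intention-to-treat population for evaluating the efficacy and safety of the planned intervention". Under Sample size calculation and statistical analyses it defines that population: "Primary endpoint analysis will be based on the intention-to-treat population, defined as all validly randomized patients". Neither sentence requires a patient to have taken study drug, and the article names no set of dosed patients.

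Schedule of assessments fixes the timing:

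- "The first study visit will be performed immediately after study participants provide written informed consent, enrolment and randomization".
- "Elective cardiac surgery will be programmed within 30 days of the first visit".
- "Doses 1–5 of study medication will be administered daily on the last 5 days before surgery", that is, on Days –5 to –1.
- The sixth dose follows within 8 hours after surgery on Day 0, and then "Doses 7–13 will be administered daily during the first 7 days after surgery".

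On collection, the same section says that "adverse events and other outcomes of interest, will be recorded in each visit". It does not say from which point an event counts towards the safety comparison. Table 2 lists three safety endpoints: adverse events, serious adverse events, and discontinuation of study medication due to adverse events.

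**The concern.** Randomisation and first dose are separated by design, and dosing is tied to the date of surgery. A patient whose operation is cancelled before Day –5, or who withdraws while waiting, takes no drug but stays in the population named for safety.

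For a superiority claim on efficacy, keeping such patients is the cautious choice because it works against the drug. For harm, the same dilution works in the drug's favour: an excess of adverse events on empagliflozin looks smaller than it is in patients who took it.

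The third safety endpoint shows the mismatch most plainly. A never-dosed patient cannot discontinue study medication because of an adverse event, yet would sit in the denominator for that endpoint.

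Safety is a declared aim of the trial. The Introduction notes that some guidelines advise against routine use of this drug class during hospital stays, and it promises key safety data in this setting.

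**Working it through.** **The plan's own size.** With 25% v 15%, one-sided α = 0.05 and 90% power, the usual two-proportion formula gives

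n = [1.645·√(2·0.20·0.80) + 1.282·√(0.25·0.75 + 0.15·0.85)]² / 0.10² ≈ 272.2, so 273 per arm (546 in total).

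Allowing for 10% dropout, 273 / 0.90 = 303.3, so 304 per arm (608 in total). Both stated figures reproduce. The 304 per arm is the intention-to-treat denominator. Nothing below changes the sample size.

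**Time from randomisation to first dose.** From Schedule of assessments: 30 days to surgery − 5 days = 25 days at most under the programmed schedule. Dosing then covers 5 + 1 + 7 = 13 days.

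**Effect of never-dosed patients.** Let f be the never-dosed share, equal in both arms. Let p₀ and p₁ be the event risks in dosed placebo and dosed empagliflozin patients, and r the risk in never-dosed patients, which does not depend on arm. Then

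- risk in arm k over all randomised = (1 − f)·p_k + f·r
- difference over all randomised = (1 − f)·(p₁ − p₀)

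The term r cancels from the difference. The documents give no value for f or for any adverse-event risk, so the inputs below are assumptions.

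| f | 5% v 10% (5-point excess) | 20% v 30% (10-point excess) |
|---|---|---|
| 1% | 4.95 | 9.9 |
| 2% | 4.90 | 9.8 |
| 5% | 4.75 | 9.5 |
| 10% | 4.50 | 9.0 |

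A set of patients with at least one dose restores 5 and 10 points.

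The crude rates and the ratio do depend on r. For 5% v 10% at f = 10%:

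- r = 0 (never-dosed patients have no recorded event): 4.5% v 9.0%, risk ratio 2.00. Both rates fall and the ratio is unchanged.
- r = 5% (never-dosed patients keep the placebo risk, for example because they still have surgery): 5.0% v 9.5%, risk ratio 1.90. The placebo rate is unchanged and the contrast shrinks.

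**Pre-dose events, only if they are counted.** Suppose a patient has an event before the first dose with probability q, the same in both arms and independent of later events. The risk per arm is then 1 − (1 − q)(1 − p). For 5% v 10%, where the true ratio is 2.00:

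| q | Rates | Difference (points) | Risk ratio |
|---|---|---|---|
| 2% | 6.90% v 11.80% | 4.90 | 1.71 |
| 5% | 9.75% v 14.50% | 4.75 | 1.49 |
| 10% | 14.50% v 19.00% | 4.50 | 1.31 |

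Both rates rise, the difference shrinks by the factor (1 − q), and the ratio moves towards 1.

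**The case against.** The best reply has four parts.

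1. **The article fixes a population and nothing more.** It gives no event window, start of counting or denominator convention, and an article commonly leaves these to the full protocol or analysis plan. Recording an event at a visit is not the same as counting it. This stands. A reader might infer that the plan counts pre-dose events against the assigned arm, but the text does not say so. That part of the point is therefore conditional. The population itself is stated, and an analysis plan that used a dosed set as its main safety set would depart from that sentence.

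2. **The size is unknown and probably small.** A reader might take the 10% dropout allowance as the never-dosed share. The documents do not support that: it is an overall allowance in the sample-size calculation, and dropout may occur after dosing or during the 90-day follow-up. At 1% to 2% the loss is slight. No safety test or margin is stated that such a shift could reverse.

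3. **Crude rates need not fall.** A reader might infer that every adverse-event rate shrinks by the never-dosed share, or that waiting time dilutes the rates. The first holds only if undosed patients have no recorded events. The second holds only for rates per person-time, which the article does not propose. In simple proportions, pre-dose events raise both arms.

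4. **Safety by randomised arm preserves the randomised comparison.** Because allocation is blinded, loss before dosing should be balanced. This also stands, and it means that the effect is attenuation and not a bias that differs by arm. It supports showing that analysis as a supplement. The word primary in the article's sentence leaves room for a second set, but it makes the randomised set the main one for safety.

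**Conclusion.** The point holds in a limited form. The article makes all randomised patients the primary population for safety, in a design where a patient may wait up to 25 days for the first dose and may never receive one. The between-arm difference in adverse-event risk is then (1 − f) times the difference in dosed patients, so a 5-point excess becomes 4.95 to 4.50 points for f from 1% to 10%. The effect is modest but anti-conservative for harm.

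This rests on an assumed never-dosed share, taken as equal in the two arms, and on undosed patients having the same event risk in both arms. The pull of the risk ratio towards 1 through pre-dose events applies only if such events are counted. The 25 days is the programmed maximum and not an average; a postponed operation could lengthen it.

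**What to change.** Amend the sentence under Randomization, stratification and blinding so that the intention-to-treat population serves efficacy only. Define the primary safety set as all patients who took at least one dose of study medication, analysed by treatment received, with events counted from the first dose onward. List events between randomisation and first dose separately, and report the number never dosed in each arm. If wanted, show safety by randomised arm as a supplement.

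The cost is one further analysis set and a slightly smaller safety denominator. No new data, visits or patients are needed, and the sample size does not change. The set should be fixed before unblinding.
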